#### **Outcomes:**

Primary Outcome: Proportion of correctly identified STEMI. ECGs will be adjudicated by a senior clinician at John Hunter Hospital in consultation with the treating clinician who has assessed the patient. All ECGs performed on all patients presenting with possible ACS will be analysed. In HNELHD, this will be performed via CAP online.

Secondary outcomes: In-hospital, 30-day and 12-month mortality, time to reperfusion (for STEMI), length of hospital stay, MACE (major adverse cardiac events: death, repeat MI or all-cause readmission) at 30-days and 12-months. Post discharge health care utilisation and medication adherence will likely be improved by better hospital care, so we will assess this by MBS and PBS linkage. Myocardial infarction will be defined by elevated troponin in the context of typical ischaemic symptoms. Mortality will be ascertained from the National Death Index (NDI). Readmissions will be captured by CHeReL. Reperfusion and revascularisation data will be ascertained from the Cardiac and Stroke Outcomes Unit in HNE.

**Measures:** Primary and secondary outcome data will be obtained from medical records and from CHeReL. We have discussed the project and received a formal quote from CHeReL. We will also link with MBS and PBS to assess post-discharge healthcare utilisation and medication prescription/adherence after hospitalisation. This will contribute valuable qualitative information as well as informing cost effectiveness analysis.

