**Allocation to treatment:**

Intervention arm - All patients presenting to an intervention hospital will have an ECG and serum troponin level result transmitted to a central reporting service based at John Hunter Hospital. This service is monitored by the Department of Cardiology at John Hunter Hospital. Staff with clinical expertise from the central reporting service will review the ECG and serum troponin level and determine the likelihood of an acute coronary syndrome. The central reporting service will contact the hospital with diagnostic support and advice on which evidence-based pathway to follow – the SCRS for STEMI or the NSW Chest Pain Pathway for non-STEMI. This utilises existing evidence-based pathways, rather than providing *ad hoc* advice on individual patient management. The service will be staffed by the clinical cardiac liaison officer of John Hunter Hospital on weekday morning shifts and by a dedicated afternoon shift and weekend clinical nurse consultant. Overnight will be staffed by the John Hunter CCU charge nurse. There is considerable experience at John Hunter Hospital with reading pre-hospital ECGs and discussing cases with the ambulance personnel who transmitted the ECG, as part of the SCRS. This project will extend this approach into rural hospitals and will also incorporate the results of troponin testing, thereby capitalising on existing expertise. This will facilitate expert ECG reading, even when the algorithm does not detect STEMI, as well as helping clinicians identify high risk ACS.

Control arm- Will continue with current practice and treatment processes which will consist of management of patients without supportive expert advice, except where this is requested as part of normal process.

**Communication between referral hospital and central reading service:** Using the iPIMS patient registration system, an automated notification to the reading clinician is generated when anyone is triaged with diagnoses compatible with acute coronary syndromes. All ECGs and point of care troponins are available on the centralised medical record (Clinical Applications Portal - CAP). The reading clinician will contact the rural hospital emergency department and will discuss the case with the treating clinician, whilst able to simultaneously view the results of troponin and ECG on CAP.

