The System Implementation Group will be chaired by the Head of Cardiology at John Hunter hospital. It will be comprised of clinicians, including the chief investigator, and operational staff to ensure stakeholder communication and address system problems. This group will meet on a fortnightly basis to oversee individual clinical cases and system development. Importantly, this group will also provide feedback to the clinicians reading the ECG and troponin results, at both an individual case level and at the aggregated data level, to maintain optimal adherence to the process.

A clinical events committee (CEC) of experienced cardiologists will also adjudicate all clinical events in a blinded fashion at Monash University. As blinding will not be possible with the system implementation group who review outcomes, scientific rigour demands a blinded review to confirm events. Monash will also provide an ECG core lab reading service. This will provide the most rigorous oversight of the trial. Disagreements on ECG reading will be resolved by consensus at Implementation Group meeting.

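### The adjudication rule for the primary outcome creates unrequested expert contact about control-hospital ECGs, with no limit on timing or on returning the reading

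*Protocol*

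**What the plan says.** **Primary outcome (Protocol, Outcomes).** The outcome is the proportion of STEMI correctly identified. On the reference reading: "ECGs will be adjudicated by a senior clinician at John Hunter Hospital in consultation with the treating clinician who has assessed the patient". On scope: "All ECGs performed on all patients presenting with possible ACS will be analysed". Neither sentence is limited to one arm.

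**Intervention (Protocol, Allocation to treatment).** ECG and troponin results are "transmitted to a central reporting service based at John Hunter Hospital". Then: "The reading clinician will contact the rural hospital emergency department and will discuss the case with the treating clinician".

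**Control (same section).** Current practice, described as "management of patients without supportive expert advice, except where this is requested as part of normal process".

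**Second layer of review (Protocol, Governance structure).** "A clinical events committee (CEC) of experienced cardiologists will also adjudicate all clinical events in a blinded fashion at Monash University". "Monash will also provide an ECG core lab reading service". "Disagreements on ECG reading will be resolved by consensus at Implementation Group meeting". The section acknowledges that the implementation group cannot be blinded.

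**The concern.** The active ingredient of the intervention is a conversation about the ECG between a clinician at the hub hospital and the rural treating clinician. The outcome rule prescribes a conversation with the same two ends, and as written it applies in control hospitals too. It is started by outcome measurement, so the exception for advice requested in normal practice does not cover it.

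Allocation is by hospital, so a clinician consulted about one control patient may well manage later trial patients. The Background section attributes 70% of missed STEMI cases to failure to interpret the ECG. Discussing a case with an expert reader could improve that very skill. At stake are whether the comparator remains usual care and whether the planned 16-point difference keeps its full size.

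**Working it through.** **1. The two contacts side by side**

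| | Intervention contact | Adjudication contact |
|---|---|---|
| Hub-side party | Reporting service at John Hunter Hospital | Senior clinician at John Hunter Hospital, not said to belong to the service |
| Rural party | Treating clinician | Treating clinician |
| Material | ECG and troponin on CAP | ECG, via CAP |
| Arms | Intervention only | No restriction stated |
| Timing | During care, after an automated triage notification | Not stated; the wording implies the patient has already been assessed |
| Advice or reading given | Diagnostic support and choice of pathway | Not stated |

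The overlap lies in the first three rows. The last two decide whether it does harm, and the Protocol leaves both open.

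**2. Two readings of the timing**

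- Contact before the diagnosis is recorded: a control patient receives something close to the intervention.
- Contact afterwards: the index patient's classification is already fixed. Only carry-over to later patients remains.

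**3. How often it could happen**

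Inputs are from Statistical methods and analysis; an equal split between arms is assumed.

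- All suspected ACS: 6,300 × 15/12 ÷ 2 ≈ 3,900 control presentations.
- Planned STEMI sample: 338 ÷ 2 = 169 control STEMIs; 169 × 0.36 ≈ 61 missed. Over 13 of the 26 planned clusters, 61 ÷ 13 ≈ 4.7 per hospital.

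Contacts about missed STEMI would therefore be few per hospital. Contacts about all ECGs, read literally, would be many.

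**4. The plan's own sample size**

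The plan gives 140 per arm for 36% v 20% missed, 80% power, p = 0.05. The standard two-sided formula gives 123 per arm, or 135 with continuity correction. So 140 is not reproduced exactly, but it errs on the safe side. Similarly, clusters of 13 with ICC 0.015 give a design effect of 1 + 12 × 0.015 = 1.18, not the stated 1.24. Neither difference bears on this point.

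**5. Illustration of dilution**

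Power = Φ{[d − 1.96·√(2p̄(1−p̄)/n)] / √[(p₁(1−p₁)+p₂(1−p₂))/n]}, with d = p₁ − p₂, p̄ the mean of the two rates, p₂ = 0.20, and a two-sided 0.05 test (sidedness is not stated; two-sided assumed).

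At n = 140 per arm, unadjusted for clustering:

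- p₁ = 0.36: (0.16 − 1.96 × 0.0537)/0.0528 = 1.04, power 0.85
- p₁ = 0.34: power 0.75
- p₁ = 0.32: (0.12 − 1.96 × 0.0524)/0.0519 = 0.33, power 0.63
- p₁ = 0.30: power 0.49

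At N = 338, using 169 ÷ design effect as the effective number per arm:

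| Control miss rate | Share of the 16-point effect gained by control | Power, design effect 1.24 | Power, design effect 1.18 |
|---|---|---|---|
| 36% | 0 | 0.84 | 0.86 |
| 34.4% | 10% | 0.77 | 0.79 |
| 32% | 25% | 0.62 | 0.64 |
| 28% | 50% | 0.34 | 0.35 |

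**6. What an average of 32% would require**

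If learning starts at nothing and grows linearly, an average of 32% needs a final rate of 28%, since (36 + 28)/2 = 32. By the end of recruitment, control clinicians would have to have gained 8 of the planned 16 points. That is a lot to expect from occasional retrospective contact. The lower control rates are chosen values; nothing in the Protocol predicts them.

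**The case against.** A reader might infer that the rule delivers the intervention to the control arm and that the contrast therefore shrinks. The text does not support that as fact, for these reasons:

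- **Timing.** The rule sits under Outcomes and refers to a clinician whose assessment is complete. Outcome data come from medical records and are recorded at discharge or transfer, and the ECG work is done online through CAP. This favours contact after the diagnosis is recorded.
- **Content.** Consultation may mean only that the adjudicator obtains clinical context. Nothing says the reading is returned. The case-level feedback that Governance structure does prescribe goes to the hub's readers.
- **Kind of contact.** The intervention is triggered at triage, runs in real time and directs the patient to a pathway. None of this is stated for adjudication.

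A reader might also infer that the trial's result must be biased toward no effect. Expert input to controls would push that way, but other forces arise from the same sentence. A reference reading made at the hub hospital could agree too readily with the hub's own reading in the intervention arm. A treating clinician who influences the adjudication could hide misses. The net direction is open.

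These objections limit the claim without removing it. The Protocol states a rule of contact, applies it to both arms and adds no safeguard. The Monash committee and core lab do not withdraw that contact.

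It can also be said that barring contact in both arms goes further than protecting controls requires. But a rule for one arm only would make outcome measurement differ between arms, so a common rule is preferable.

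**Conclusion.** The point holds in limited form. As written, the outcome rule conflicts with the definition of the control arm, because it requires unrequested contact between an expert at the hub hospital and control clinicians about their ECGs. On the more likely timing, the consequence is possible carry-over learning during about 15 months of recruitment.

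That mechanism would narrow the contrast by an amount that cannot be derived from the Protocol. The fall in power from about 0.85 to 0.63 rests on an assumed control miss rate of 32%, 140 per arm, a two-sided 0.05 test and no allowance for clustering. It shows how sensitive the trial would be to dilution and is not a forecast. No conclusion about the net direction of bias follows. This is an inexpensive improvement to the primary comparison.

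**What to change.** In the Protocol, Outcomes:

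1. Delete the clause that has the adjudicator consult the treating clinician.
2. State that in both arms adjudication takes place after the episode has closed, from the ECG, troponin and notes held on CAP.
3. State that no case-level adjudication result goes to control hospitals during recruitment, except through existing routine clinical governance.
4. Reconcile this with Governance structure: say how the hub clinician's reading relates to the Monash core lab reading, and how the disagreement rule fits, given that it refers cases to an implementation group that cannot be blinded.

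The change is to wording only; the ECGs and troponins are already on CAP and a core lab is already planned. The cost is that the adjudicator loses verbal clinical context and relies on the record. The same deletion removes the treating clinician's influence on the reference diagnosis.

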#### **Statistical methods and analysis:**

- 1) Power calculation: Based on local data, anticipated number of presentations to hospital with suspected ACS over a 12-month period are approximately 6,300. Of these an estimated 50% will require admission and investigation for ACS. Around 15% of the total patient group will have non-STEMI and a further 5% have STEMI, i.e. ~315 STEMI per year across all centres. An estimated 36% of the patients with STEMI will be missed and we wish to detect an absolute reduction in missed STEMI of 16%, i.e. 36% down to 20%, which will require 280 participants (140 per arm), at 80% power and  $p=0.05$ . We also include a design effect of 1.24 (assuming cluster sizes of 13 and  $ICC=0.015$ ) for a total of 338 patients across 26 clusters total. Therefore, it will take approximately 15 months to recruit. In the two-year timeframe, we will be able to analyse the rate of STEMI detection (primary endpoint) and will have a *median* 12-month follow-up for the secondary endpoints.
- 2) Evaluation of Results: Analysis of the primary outcome (the proportion of correctly identified STEMI) will be via logistic regression with adjustment for stratifying variables (size and staffing of hospital), and analysis of the secondary outcomes will be via linear and logistic regression.
- 3) Economic evaluation: Assuming an improvement in STEMI identification, three economic evaluations will be conducted. 1) From a health provider perspective, a cost-effectiveness analysis to report the resources required per unit improvement in the identification of STEMI. Costs will include the cost of the intervention as well as related costs such as hospital stay,

treatments and readmissions. The measure of effect will be based on the primary outcome (identification of STEMI). 2) A cost-consequence analysis will report the cost of the intervention and its range of consequences such as the change in STEMI identification, reperfusion times, hospital admissions, readmissions and MIs. 3) A modelling exercise to estimate costs and potential downstream impacts from the intervention over a ten-year time frame, these will include avoided healthcare costs as a consequence of improved STEMI detection and treatment, as well as adherence to secondary prevention therapies. This will be informed by data linkage with MBS and PBS.

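### True STEMI for the primary outcome is set by ECG adjudication at the hub hospital, with no link to the protocol's own MI definition, so mimics and shared misreadings can be scored as STEMI

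*Protocol*

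**What the plan says.** The Outcomes section names the endpoint as follows: "Primary Outcome: Proportion of correctly identified STEMI". It decides which cases are true STEMI in this way: "ECGs will be adjudicated by a senior clinician at John Hunter Hospital in consultation with the treating clinician who has assessed the patient". The material named is the ECG: "All ECGs performed on all patients presenting with possible ACS will be analysed". No confirmation of infarction is required.

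The only definition of infarction stands in the next paragraph, among the secondary outcomes: "Myocardial infarction will be defined by elevated troponin in the context of typical ischaemic symptoms". Nothing links it to the primary outcome.

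Under Allocation to treatment, intervention hospitals have the ECG and troponin result "transmitted to a central reporting service based at John Hunter Hospital". Staff there "will review the ECG and serum troponin level and determine the likelihood of an acute coronary syndrome". The same section places ECGs and point-of-care troponins together on the central record.

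Governance structure adds two external resources: a blinded committee of cardiologists for clinical events, and an ECG core lab. Disagreements on ECG reading go to the Implementation Group, for which the protocol says blinding is not possible. It does not say which of these readings is the reference for the primary outcome.

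The power calculation gives the expected case mix: "Around 15% of the total patient group will have non-STEMI and a further 5% have STEMI".

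**The concern.** The primary outcome compares the rural clinician's diagnosis with a reference. In the intervention arm that clinician has been advised by an expert reader at the hub, and the reference is then set by an expert reader at the same hospital. If both take an old ST change, early repolarisation or pericarditis for STEMI, the error enters the denominator and the intervention hospital is credited with a correct identification. A control clinician who rightly did not call the same tracing is recorded as having missed a STEMI.

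Consulting the treating clinician does not repair this. That person's judgement is what is being scored, and in the intervention arm it has already been shaped by the hub.

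Blinding alone does not repair it either. A blinded reader who is not asked whether infarction was confirmed could still accept a mimic.

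At stake is the primary comparison, and also the cost-effectiveness analysis, which uses the same outcome as its measure of effect. The Outcomes section lists nothing that counts false-positive STEMI calls, so over-calling would not show elsewhere.

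**Working it through.** **The decision route, side by side**

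| Step | Who | Material named | Blinded to arm |
|---|---|---|---|
| Intervention reading | Hub at John Hunter Hospital | ECG and troponin | Not applicable |
| Primary-outcome adjudication | Senior clinician at the same hospital, with the treating clinician | ECGs | Not stated |
| Core lab | External | ECGs | Not stated |
| Disagreement on ECG reading | Implementation Group | ECG reading | Stated as not possible |
| Clinical events | External committee | Clinical events | Yes |

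No row makes troponin part of the STEMI decision, and no row gives that decision to the blinded committee.

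**Inputs from the protocol.** There are 6,300 presentations a year, 5% of them STEMI: 0.05 × 6,300 = 315, which reproduces the protocol's figure. Missed STEMI is 36% against 20%. The total is 338 patients, or 169 per arm. With cluster size 13 and ICC 0.015 the design effect is 1 + 12 × 0.015 = 1.18. The protocol prints 1.24, a separate matter. I use 1.18, so the effective size is 169/1.18 = 143 per arm and power without mimics is 86% (84% with 1.24). The protocol's unadjusted 280 is not reproduced: the two-sided formula gives 246, or 270 with continuity correction. That does not bear on this point.

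**Assumed, because the protocol gives nothing.** Let f be the share of mimics among reference STEMI, and let q be the proportion of mimics not called STEMI (q_C control, q_I intervention). Let m_C and m_I be the missed proportions among true STEMI.

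**Formula.** Apparent missed proportion = (1 − f)·m + f·q. The apparent reduction is therefore

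(1 − f)(m_C − m_I) + f(q_C − q_I).

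Mimics inflate the true effect only when q_C − q_I exceeds m_C − m_I. Otherwise they dilute it.

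**Case A: no true effect, unequal calling.** Set m_C = m_I = 0.36 and q_I = 0.10. The apparent reduction is f(q_C − 0.10). For f = 10% and q_C = 0.80:
- control: 0.9 × 0.36 + 0.1 × 0.80 = 0.404
- intervention: 0.9 × 0.36 + 0.1 × 0.10 = 0.334
- difference: 7.0 points

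| f | q_C = 0.36 | q_C = 0.60 | q_C = 0.80 | Chance of a significant result (nominal 5%) |
|---|---|---|---|---|
| 5% | 1.3 | 2.5 | 3.5 | 6% to 9% |
| 10% | 2.6 | 5.0 | 7.0 | 8% to 23% |
| 20% | 5.2 | 10.0 | 14.0 | 15% to 69% |

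**Case B: true effect 36% to 20%, mimics called equally.** The reduction is 0.16(1 − f).

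| f | Apparent reduction (points) | Power, for q from 0.36 to 0.80 |
|---|---|---|
| 0 | 16.0 | 86% |
| 5% | 15.2 | 80% to 82% |
| 10% | 14.4 | 74% to 77% |
| 20% | 12.8 | 61% to 66% |

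**How large f might be.** One arm-year has 3,150 presentations: 157.5 STEMI and 2,992.5 others. If the reference wrongly labels 0.5%, 1% or 2% of the others, there are 15.0, 29.9 or 59.9 mimics. Then f = 15.0/172.5 = 8.7%, 29.9/187.4 = 16.0%, or 59.9/217.4 = 27.5%. If control clinicians call 20% of mimics and hub-supported clinicians 80%, with no true effect, the spurious differences are 0.6f = 5.2, 9.6 and 16.5 points. If hub-supported clinicians call 50%, they are 0.3f = 2.6, 4.8 and 8.3 points.

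The 2% case does not fit the planning figures. It puts control missed STEMI at (0.36 × 157.5 + 0.80 × 59.9)/217.4 = 48% and adjudicated STEMI at 217.4/3,150 = 6.9% of presentations, against the protocol's 36% and 5%.

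**The case against.** The strongest reply is that the reference is not a bare tracing. The adjudicator speaks to the clinician who saw the patient and works through a record that also holds the troponins. The Measures paragraph says that primary-outcome data come from medical records. All ECGs are analysed, so tracings can be compared. The hub also sees troponin and may decline to call a troponin-negative mimic. A blinded committee and an external core lab exist. An ECG-centred reference also suits an intervention aimed at ECG misreading, which the Background reports in 70% of missed STEMI. Detailed ECG criteria may stand in a SAP that is not shown.

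Much of this stands. A reader might infer that mimics do enter the denominator, that the bias always favours the intervention, or that it could equal the 16-point target. The documents support none of these. They give no mimic rate and no call rates, the hub's troponin may narrow or reverse the contrast in calling, and equal calling dilutes the effect. Nor is there a clear contradiction over MI, because the definition may be meant only for repeat MI within MACE. The documents also do not say that the core lab sees the tracing alone. I do not count missing ECG thresholds as a fault.

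A rule that demanded positive confirmation of every case would be wrong too. Later samples and angiography are likelier in patients who were identified and transferred, so missed patients sent home would drop out, probably more often in the control arm.

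What the reply leaves open is the link itself. Access to troponin is not a criterion, and the blinded committee is not given the STEMI decision.

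**Conclusion.** The point holds in a limited form. What counts as a true STEMI defines the primary endpoint, and the protocol already fixes a route to it: ECG adjudication at the hub hospital, with the scored clinician consulted, no tie to the protocol's MI definition, and ECG disagreements sent to a group that cannot be blinded. That route allows error shared between hub and reference to be credited in one arm only.

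The size is unknown. With mimics at 5% to 10% of reference cases, the illustrations give 1.3 to 7.0 points of spurious reduction under unequal calling, or a loss of 0.8 to 1.6 points from a true 16 under equal calling. These rest on assumed mimic shares and call rates, and on a 36% missed rate among true STEMI. The direction depends on whether the hub raises the calling of mimics. This should be corrected, but it does not show that the trial's result would be wrong.

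**What to change.** In the Outcomes section, write one reference definition:

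- Reference STEMI is a qualifying ECG in a patient who meets the protocol's MI definition on the record of the whole episode, including the receiving hospital's samples.
- A case with a qualifying ECG is removed only when adequate serial troponins positively exclude MI. State what counts as adequate.
- A case with no adequate later sample, including early death or discharge, stays in the denominator, so that missed patients are not lost differentially.
- The existing blinded events committee decides in both arms, using the core-lab ECG reading, without being told the arm or the initial diagnosis by the hub or the treating clinician. Disagreements are settled there, not in the Implementation Group.
- The ECG-only version is reported as a sensitivity analysis, with the number of cases kept for want of a sample shown by arm.

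The cost is mainly wording, because the ECGs, point-of-care troponins, committee and core lab are already in the plan. It adds some adjudication work and makes the denominator slightly smaller. Some mimics will remain: certain conditions raise troponin without STEMI, and unsampled cases are kept by design.

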**Research Question:** In patients admitted to a rural hospital with suspected ACS, does a centralised management system improve identification of STEMI and subsequent clinical outcomes in all ACS patients?

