**Participants:** All patients presenting with chest pain for investigation to hospitals from rural and remote communities throughout the HNELHD. Notably, patients with prehospital ECGs performed by ambulance paramedics showing STEMI will NOT go through this process, they will go via existing SCRS pathways. All patients presenting to Emergency Departments, whether by self-transport or via ambulance without a prior STEMI diagnosis, will be included.

**Eligibility:** Inclusion criteria – Hospitals where GPs or Career Medical Officers (CMOs) manage ACS presentations will be included. All consecutive patients presenting to hospital with suspected ACS (eg. chest pain for investigation or other heart related symptoms such as shortness of breath or who are triaged as possible ACS) will be included.

Exclusion criteria – Hospitals staffed by Emergency Medicine specialists (FACEMs) will not be included. Our data suggest the rate of missed STEMI in these hospitals is low. There will be no patient-level exclusion criteria.

**Randomisation:** Hospitals will be randomised to receive the intervention (MORACS) or control (usual care). Randomisation will be undertaken independently by personnel from the HMRI statistical support unit. Randomisation will be stratified based on hospital size and medical staffing. Rural hospitals included in the study have bed numbers that range from 0 to 100. In most rural hospitals admissions are managed by on-call GPs where the GP attends as required. In a small number of rural hospitals admissions are managed by CMOs who are staffed 24 hours per day, therefore potentially able to offer more timely treatment. GP vs CMO staffing will be separately stratified to better identify different outcomes of care driven by differing medical management system in place.

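### The primary denominator is formed after open hospital randomisation, from site suspicion and ECGs performed, so control-arm STEMIs may go uncounted; the text also contradicts itself on admission and exclusions

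*Protocol*

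**What the plan says.** The Outcomes section gives "Primary Outcome: Proportion of correctly identified STEMI" and adds that "All ECGs performed on all patients presenting with possible ACS will be analysed". It gives no other rule for which STEMIs form the denominator.

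Entry to the cohort is set in the Eligibility paragraph: "All consecutive patients presenting to hospital with suspected ACS". The examples that follow are chest pain, other heart-related symptoms such as "shortness of breath or who are triaged as possible ACS) will be included". The Participants paragraph is narrower and names chest pain only.

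Under Allocation to treatment, "All patients presenting to an intervention hospital will have an ECG and serum troponin level result transmitted" to the hub, while control hospitals carry on with current practice. The hub is alerted by a notification that "is generated when anyone is triaged with diagnoses compatible with acute coronary syndromes".

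On the population, the Research Question reads "In patients admitted to a rural hospital with suspected ACS". The project summary, Hypothesis 2, Participants, Eligibility, Outcomes and the power calculation all speak of patients who present. The Eligibility paragraph says "There will be no patient-level exclusion criteria", yet the Participants paragraph just before it leaves out patients whose ambulance ECG already showed STEMI.

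**The concern.** Hospitals are randomised, but the patients who supply the primary outcome are found afterwards, by staff at those hospitals. The protocol does not say that rural staff know their allocation, but a hub that telephones the emergency department cannot be hidden from them. If the service changes who is suspected of ACS or who gets an ECG, it changes which STEMIs are counted as well as how many are identified. This is identification bias in a cluster trial.

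The likely direction follows from the process. A control patient with a STEMI who is never suspected, or who has no ECG that shows it, leaves both numerator and denominator. The control missed rate then looks lower than it is and the contrast shrinks.

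The conflicts over the population bear on the same denominator. The power section expects only 50% of presenters to need admission. Read literally, the Research Question would drop a missed STEMI that was sent home, which is an event the trial exists to count.

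**Working it through.** **Inputs from the protocol (power calculation).** 6,300 presentations a year; STEMI in 5%; missed rate 36% in control and 20% with the intervention; 140 per arm at 80% power; design effect 1.24; 338 patients in total. A two-sided test at 0.05 is assumed, since sidedness is not stated.

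**The plan's own figures.** 6,300 × 0.05 = 315 STEMI a year, as stated, so the plan counts presentations and not admissions. For 36% v 20%, the pooled-variance formula gives 123 per arm at 80% power (135 with continuity correction) and 140 per arm at 85%. The stated 140 is therefore not reproduced at 80% power, but it is not short. With 338/2 = 169 per arm, the effective size is 169/1.24 ≈ 136 per arm.

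**Baseline power.** Power = Φ[(d − 1.96·SE₀)/SE₁], with SE₀ from the pooled rate and SE₁ from the separate rates. Here d = 0.16. SE₀ = √(0.28 × 0.72 × 2/136) = 0.0545. SE₁ = √((0.36 × 0.64 + 0.20 × 0.80)/136) = 0.0536. Power = Φ(0.99) = 84%.

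**Effect of uncounted control misses.** Let u be the share of control missed STEMIs that never enter the count, with none lost in the intervention arm. The protocol gives no value for u, so the range is an assumption. The observed control missed rate is 0.36(1 − u)/(1 − 0.36u).

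| u | Observed control rate | Difference from 20% | Power, 136 per arm held | Power, control arm reduced by the lost cases |
|---|---|---|---|---|
| 0 | 36.0% | 16.0 points | 84% | 84% |
| 10% | 0.324/0.964 = 33.6% | 13.6 | 72% | 71% |
| 20% | 0.288/0.928 = 31.0% | 11.0 | 55% | 54% |
| 30% | 0.252/0.892 = 28.3% | 8.3 | 36% | 34% |

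The difference vanishes when 0.16 = 0.288u, that is u = 55.6%. The protocol's cluster size of 13 and ICC of 0.015 give a design effect of 1 + 12 × 0.015 = 1.18. Using that in place of 1.24 raises these powers by about 2 points.

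**Equal loss in both arms.** With 20% of misses uncounted in each arm, the rates are 31.0% and 0.16/0.96 = 16.7%. The difference is 14.4 points and power is about 80% (78% if both arms are reduced by the lost cases). With 30% in each arm the difference is 13.4 points. The damage comes from unequal loss.

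**Safeguards in the text.** The centralised record holds every ECG that was done, but cannot supply one that was not. The blinded ECG core lab and clinical events committee (Governance structure) classify ECGs and events and do not decide who enters. Linkage is described for readmission and death, and no rule uses it to find missed STEMI.

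**The case against.** The case against a large effect is substantial, and most of it stands.

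- A reader might infer that ECGs are mandated in intervention hospitals only, or that control patients go without. The text does not support this. It mandates transmission and only implies an ECG. Nothing says that controls lack ECGs, and the sentence on analysing ECGs has no arm restriction. A control STEMI that was recorded but misread is counted, provided the patient is in the cohort.
- The Background attributes 70% of missed STEMI to failed ECG interpretation, which presupposes an ECG. On those data at most 30% of misses could lack one. They cover only misses that came to light, however, and do not speak to patients who were never suspected.
- Entry is by symptoms or by triage, not by triage alone. The triage-diagnosis wording describes the hub alert.
- The Measures paragraph names medical records and linked data as sources for primary and secondary outcomes together. It still gives no linkage rule for the primary denominator.
- *Admitted* defines the population only in the Research Question, and no operative text drops patients sent home.
- A reader might infer that counting paramedic-identified STEMI will dilute the effect. The Participants paragraph leaves these patients out of both arms alike, so the fault is a contradictory statement and not a quantified loss of power.
- It is also tempting to call the uncounted cases the most serious misses. Nothing in the protocol shows that.
- The bias described runs towards no effect, so it would not by itself create a false positive.

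What remains is that suspicion and ECG recording both happen after open allocation, under different processes by arm, and no stated safeguard recovers a STEMI lost at either step.

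**Conclusion.** The concern holds as a risk of identification bias of unknown size, together with two plain contradictions about the primary population. The illustrative fall in power from about 84% to 72, 55 or 36% rests on assumed one-sided losses of 10, 20 or 30% of control misses. The protocol gives no figure for such losses, and the 30% case is the ceiling that its own data allow for misses with no ECG. If losses are similar in the two arms, most of the 16-point difference survives. The documents do not show that the bias will occur. They show that it could, and that the plan as written would not reveal it.

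The contradictions, *admitted* against *presenting* and no exclusions against the prehospital-STEMI carve-out, need no assumption. They should be corrected because they define who is counted.

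**What to change.** 1. In the Research Question, change *admitted* to *presenting*, to match the rest of the protocol and the 315 STEMI a year.
2. List prehospital-identified STEMI as the one patient-level exclusion, and remove the statement that there is none.
3. Replace the two entry definitions with one list of presenting symptoms. Extract the cohort centrally, blind to arm, with the same query in every hospital, whether or not the patient was admitted and whether or not an ECG was done. Do not define entry by triage diagnosis or by having had an ECG or troponin, since those are the steps that may differ by arm.
4. Report presentations and ECG rates by arm, so that differential case-finding would be visible.
5. Prespecify a sensitivity analysis using the planned CHeReL and death linkage. It would count as missed any STEMI admission or cardiac death within a fixed short window of an index presentation at a study hospital, where the blinded clinical events committee attributes the event to that presentation. This belongs in a sensitivity analysis because some linked events will be new ones, and making it primary would change the outcome.

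The cost is one central query, some attribution work for the committee, and a wait for linkage before the sensitivity analysis can be run. Presenting symptoms are still recorded by site staff, so the rule reduces dependence on allocation without removing it.
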